### Recruitment

#### Original protocol

Recruitment for this study poses several challenges because study participants include postoperative patients with delirium which makes them temporarily unable to give informed consent. In the original protocol, we planned a preoperative screening to include only patients with high risk of delirium. This was defined as the presence of at least three of the following risk factors: age ≥ 65 years, history of delirium, active smoker, consumption of at least three daily alcoholic beverages, or sensory impairment (sight, hearing). Postoperative delirium was defined as a score of ≥4 on the ICDSC [19] confirmed by a medical diagnosis of delirium recorded in the hospital chart. Since it is impossible to predict whether and when delirium will occur, two recruitment steps were planned.

Step 1 – All patients admitted to the pre-surgical unit at the study hospital will be assessed for study eligibility before their surgery by the nurse-mentor. The aim and requirement of the study protocol will be presented to eligible patients. Patients who agree will give the name of a family caregiver who will also be informed of the study. Both members of the dyad will be allowed to discuss their participation in study and sign the consent forms.

Step 2 – After surgery, if patients experience delirium, their family caregiver will be phoned by the nurse-mentor to re-confirm their initial consent, and the dyad will be included in the study. For dyads randomized to the intervention to be eligible, the caregiver must agree to participate within 24 hours of delirium onset in order to ensure a prompt start to the intervention.

Informed consent is obtained from each participant in this study.

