### Sample: eligibility criteria

Patients and family caregivers must be 18 years or older, have the ability to speak and read French, and have the physical and cognitive ability to give informed consent. Additionally, all patients must be scheduled for coronary artery bypass grafting (CABG) or heart valve surgery, must spend their full postoperative stay in the study hospital (i.e., not be transferred to another hospital), and present postoperative delirium defined by a score of 4 or higher on the Intensive Care Delirium Screening Checklist (ICDSC) [19] and confirmed by a medical diagnosis.

Eligible caregivers will be identified as such by the patient, and must be available twice daily for 3 consecutive days after delirium onset to visit the patient and receive pre- and post-bedside visit interventions.

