#### Intervention structure

The intervention structure is described in Table 1 and was based on previous studies with caregiver involvement with delirium [18, 20] or dementia [17] and on the level of involvement that was deemed acceptable to family caregivers and acute care patients who are in a precarious state after cardiac surgery. The duration of each encounter was selected to allow time for the caregiver to become comfortable with behaviors within the timeframe allowed for visiting hours and to allow time to reflect on the bedside visits. The intervention consists of a total of seven encounters involving the nurse, caregiver and patient. The first encounter will begin within 24 hours of delirium onset followed by five others at a rate of two encounters a day over the next three consecutive days. A seventh encounter will take place just before hospital discharge. The duration of each of the first six encounters is planned as follows: a pre-bedside mentoring session of 30 minutes; a 15 minute bedside visit with the patient (to abide by the ICU’s visitation hours policies); and a post-bedside session of 15 minutes. The seventh encounter before discharge will last 30 minutes. The nurse-mentor accompanying the caregiver will act as his mentor and is a nursing PhD candidate experienced both with cardiac surgery patients and delirium. In addition, she has received the same 3 hours of training offered by the research hospital to the staff on a regular basis.

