#### Randomization

Given the setting of the research center’s ICU and post-ICU surgery wards, with one visitor room shared by both surgical units as the site of the nursing intervention, participant blinding to group assignment is not possible. This poses a risk of inter-group contamination. To reduce this risk, randomization of blocks of time will be used instead of individual randomization. Two-week blocks, followed by a washout period of one week will be assigned to either the control or intervention group. Thus, if a delirium episode is detected during a 2-week block allocated to control, this patient and their caregiver will be assigned to the control group and vice versa. Participants will not be informed of the present allocation of the 2-week block of time until after they have consented to the study. Delirium episodes detected during the 1-week wash out period will not be randomized or included in the study.

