### Data collection and analysis

#### Statistical methods

The planned analyses concerning all the primary objectives include descriptive statistics, which, along with 95% CI, will be used to portray the intervention and study design’s acceptability and feasibility criteria. Control and experimental group descriptions will be achieved using descriptive statistics reflected by n, mean, standard deviation, and median, minimum, and maximum for continuous variables and frequencies and percentages for categorical variables; 95% CIs will also be presented when appropriate. Finally, to evaluate the validity of cerebral _r_SO_2_, a Pearson or Spearman correlation will be used (depending on level of measurement) to correlate oximetry scores and scores obtained on the ICDSC, DI, and CAM-ICU at Days 1, 2, and 3 following the onset of delirium.

The planned analyses for the study’s secondary objective of preliminary efficacy will include the statistical methods detailed below. It should first be noted that this is a pilot study assessing the feasibility of a larger study and statistical analyses will be used to examine the preliminary effects of the intervention and determine any trend in the results as this study is not powered for statistical testing. For H1 relative to delirium severity, a repeated measure ANCOVA will be performed using the DI scores taken on Days 1, 2, and 3 following delirium onset. The initial scores on the ICDSC taken at delirium onset will be used as a covariate. Post-hoc tests will be performed if the omnibus test is significant for the group by time interaction. Such an interaction would imply that delirium severity is different between groups over the three days. Mixed models will be used so that a patient with missing data at Days 1, 2, and 3 following the onset of delirium will not be excluded from the analysis. The intent-to-treat principle will be respected; all the patients in the study will be included in the analysis according to their group of randomization. Because the pilot study will not be used to definitely assess the efficacy of the intervention (this would be the objective of the larger study), we plan to conduct a sensitivity analysis using the last observation carried forward.

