The postoperative approach to recruitment implied specific ethical issues because patients with delirium lose their ability to give informed consent for the duration of their delirium. Given that the experimental intervention had little potential for deleterious effects, that a caregiver was involved, and that the patients would be able to consent after resolution of their delirium, the ethics committee allowed a new procedure for recruitment. This procedure included obtaining informed consent from the caregiver only during the delirium, followed by informed consent from the patient once the delirium resolved. The ethics committee’s decision was also based on a modified article of the Quebec Civil Code [52] which now allows the family to consent for the temporarily cognitively impaired parent in studies in which potential deleterious effects are minimal. This is parallel to the consent for care that can be provided by family members in clinical care settings when the ill person is unable to consent due to cognitive impairment. Therefore, in the present study, we obtain informed consent from caregivers when patients themselves are unable to consent. The patient has to consent for the study after emerging from the delirium before the time or outcome assessment at 1 month; the data collected in patients who cannot consent within that time frame are excluded from the study, as well as those for caregivers. This approach to recruiting patients is proving more effective than the initial approach.

In addition to this first challenge, our team experienced difficulty with delirium detection. In the research milieu, a delirium screening tool, the ICDSC, is administered three times a day as part of usual care for all post-surgical patients in the ICU, and as needed on the surgical ward. It was expected that delirious patients would be identified by a score of four or higher on the ICDSC, as recommended [19]. However, we observed that a number of patients with hypoactive delirium do not score four or more on the ICDSC. Hypoactive delirium is recognized by the scientific community as being highly underdiagnosed or misdiagnosed for depression because of its less behaviorally-disturbing nature [53, 54]. Until now, the most effective way to identify patients with hypoactive delirium has been to speak to all patients with a score of at least one on the ICDSC scale, and focus on identifying more subtle symptoms such as inattention or mild hallucinations.

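### Two stated rules can remove dyads after the time block has fixed their arm, so the intent-to-treat statement is not delivered as written

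*Protocol article*

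**What the plan says.** **When the arm is fixed.** Randomization is by 2-week block, and the arm follows from the block in which delirium is detected: "if a delirium episode is detected during a 2-week block allocated to control, this patient and their caregiver will be assigned to the control group" (section Randomization), with the converse for intervention blocks. Under Study limits, the envelope is opened at the start of each block. Participants are kept unaware for a time: "Participants will not be informed of the present allocation of the 2-week block of time until after they have consented to the study". The section Blinding says that the nurse-mentor, who phones the caregivers in Step 2, cannot be blinded.

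**Rule 1, 24-hour agreement.** Original protocol, Step 2: "For dyads randomized to the intervention to be eligible, the caregiver must agree to participate within 24 hours of delirium onset". The reason given is "in order to ensure a prompt start to the intervention". No time limit for agreement is stated for control dyads. Intervention structure adds, for the intervention arm, "The first encounter will begin within 24 hours of delirium onset".

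**Rule 2, patient consent by 1 month.** Preliminary feasibility results describes the procedure now in use. The caregiver consents during the delirium. The patient must consent after emerging from it and before the 1-month assessment. Otherwise "the data collected in patients who cannot consent within that time frame are excluded from the study, as well as those for caregivers".

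**The promise.** Statistical methods says that intent-to-treat will be respected and that "all the patients in the study will be included in the analysis according to their group of randomization". The same paragraph chooses mixed models so that a patient with missing daily scores is not lost from the H1 analysis.

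**The concern.** Intent-to-treat protects the comparison only if membership of the analysis set does not depend on anything that happens after allocation and could differ by arm or be related to outcome. Rule 1 tests eligibility in one arm only, and the person making the call knows the arm. Rule 2 makes membership depend on regaining capacity, which is close to what H1 (delirium severity) and H4 (psycho-functional recovery) measure. It also discards caregiver data for H5 and H6, although caregivers consent for themselves.

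At stake are the effect trends that the pilot is meant to show and the retention figures that a larger trial would be planned on. The study design is itself under evaluation in the primary objective, so a mismatch between the stated and the actual analysis set matters even in a pilot.

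**Working it through.** **The plan's own figure.** The article gives no rate for late agreement or failed patient consent. Its one precision figure, for caregiver consent, reproduces: 1.96 × √(0.75 × 0.25 / 30) = 0.155, the stated ± 15.5%. It is not in dispute here and does not describe losses after allocation.

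**Side by side: Rule 1 and the arm.**
- Randomization fixes the arm when delirium is detected, before the caregiver has agreed.
- Step 2 then sets a condition on dyads already described as randomized to the intervention.
- The stated reason, a prompt start of the intervention, has no counterpart in control.
- The amendment replaces preoperative screening and consent with postoperative consent. It does not say whether the 24-hour condition continues.

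**Side by side: Rule 2 and the promise.**
- Delirium Index scores for H1 are taken on Days 1 to 3 (Table 1). They exist by the time patient consent is sought, which Table 1 places at discharge.
- A patient who misses one of those days stays in the H1 model. A patient with all three days but no consent by 1 month does not.
- Table 1 lists caregiver consent separately, at enrolment. Caregiver anxiety and self-efficacy (H5, H6) are caregivers' own outcomes. Each dyad dropped costs 1/30 = 3.3% of the planned caregiver sample.
- The promise covers patients in the study. It can be met literally only because the removed dyads are defined as outside the study.

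**Illustration of size; every input below except the 0.05 level is an assumption.** 15 dyads per arm (time blocks do not guarantee this), no true effect, outcome SD 1 with higher meaning worse, two-sided t-test at 0.05, 20,000 simulated trials. The dyads removed are those highest on a propensity that has correlation ρ with the outcome. A negative bias flatters the intervention.

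| Removed (intervention, control) | Bias in SD / type I error, ρ = 0 | ρ = 0.5 | ρ = 1 |
|---|---|---|---|
| 0, 0 | 0.00 / 0.050 | 0.00 / 0.050 | 0.00 / 0.049 |
| 1, 0 | 0.00 / 0.048 | −0.06 / 0.054 | −0.12 / 0.068 |
| 2, 0 | 0.00 / 0.049 | −0.12 / 0.066 | −0.23 / 0.107 |
| 3, 0 | 0.00 / 0.048 | −0.16 / 0.074 | −0.33 / 0.156 |
| 4, 0 | 0.00 / 0.046 | −0.21 / 0.083 | −0.42 / 0.219 |
| 3, 1 | 0.00 / 0.051 | −0.10 / 0.064 | −0.21 / 0.123 |
| 2, 2 | 0.00 / 0.050 | 0.00 / 0.055 | 0.01 / 0.084 |

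Bias needs both a difference between arms and a link to outcome. Equal removal leaves the difference unbiased, although trimming one tail raises type I error somewhat when the link is strong. By symmetry, removing more controls reverses the sign. For scale, the standard error of the difference is √(1/15 + 1/15) = 0.37 SD.

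**The case against.** **Status of the 24-hour rule.** It stands under Original protocol and is tied to re-confirming a preoperative consent that the amended procedure no longer requires. It may have lapsed. The 24-hour start under Intervention structure is a delivery target, not an eligibility test. This stands in part: the article leaves the rule's status open, and that needs settling. Rule 2 is current in any case and conflicts with the promise on its own.

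**Symmetry already built in.** Caregivers in both arms must be available twice daily for 3 days from onset, and Table 1 puts caregiver consent and baseline measures at onset for everyone. A control caregiver who agreed late would miss that schedule. Participants also consent before learning their allocation. This narrows the asymmetry considerably but does not remove it: only intervention dyads become ineligible on a stated clock, and the caller is unblinded.

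**Ethics.** Rule 2 belongs to the consent procedure that the ethics committee allowed, and on its face it applies equally to both arms. That stands. The plan cannot simply analyse data it has no consent to use. It can name the analysis set correctly and ask what may be kept.

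**Transparency.** Table 4 records difficulties with patient consent, reasons for refusal after the episode and reasons for withdrawal. A detailed flowchart is promised. These would help show losses but do not restore intent-to-treat.

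**Stronger readings that the article does not support.** A reader might infer that the control arm holds slow or unavailable caregivers while the intervention arm does not; the common availability criterion speaks against that. A reader might infer that the sickest patients disappear at different rates by arm; the article gives no rates and does not discuss death in this context. A reader might infer that feasibility is overstated; the primary indicator is consent among caregivers approached, which these exclusions do not alter. A reader might add the criterion that patients "must spend their full postoperative stay in the study hospital (i.e., not be transferred to another hospital" as a third exclusion; nothing says that a transferred patient's data are dropped, and a planned care pathway is a natural reading.

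**Conclusion.** The point holds in a limited form. As written, Rule 2 conflicts with the intent-to-treat statement, and Rule 1 adds a one-arm condition if it is still in force. The link between failing to consent and outcome is an inference, though a close one, because consent requires emerging from delirium.

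Size and direction are unknown. The illustration shows a range from no bias, when removal is unrelated to outcome, to about 0.4 SD when four intervention dyads are removed strictly by worst outcome. Those inputs are assumed. Neither rule alone is shown to supply both conditions for bias: Rule 1 can supply the difference between arms, and Rule 2 the link to outcome. Most of the illustrated shifts are smaller than one standard error of the difference.

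Efficacy is a secondary objective that the article calls unpowered, so the weight is moderate. The point deserves action because the pilot tests the design for a larger trial and the correction is cheap.

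**What to change.** 1. State whether the 24-hour agreement condition is in force. If it is, apply the same window in both arms. Cost: a wording change, and possibly a few late control dyads lost.
2. Keep consenting caregivers' own data (H5, H6 and feasibility indicators) whatever the patient's consent status, subject to ethics committee agreement.
3. Ask the ethics committee whether patient data already collected under caregiver consent may be kept when the patient dies or does not regain capacity. Cost of items 2 and 3: a short amendment request.
4. Describe the patient analysis set as modified intent-to-treat (consented dyads) in Statistical methods. In the promised flowchart, report all allocated dyads and every post-allocation exclusion by arm, with the reason. Cost: wording, and a few extra lines in the flowchart.

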#### Anticipated recruitment time

On average, 28 patients per week undergo CABG surgery or cardiac valve surgery with post-surgical recovery in the research hospital. A 40% incidence of delirium is estimated, which represents approximately 11 patients weekly. Our team’s past experience in the same research milieu with a study involving family caregivers in a highly similar context showed a recruitment rate of 30% [49]. Thus, a recruitment rate of one to two dyads weekly is expected and a total of 20 weeks is planned to reach a sample size of 30 dyads.

### Allocation

#### Sequence generation

The randomization scheme will be automatically generated by a coordinating center, and block of time allocation will be carried out using sealed, opaque envelopes.

#### Randomization

Given the setting of the research center’s ICU and post-ICU surgery wards, with one visitor room shared by both surgical units as the site of the nursing intervention, participant blinding to group assignment is not possible. This poses a risk of inter-group contamination. To reduce this risk, randomization of blocks of time will be used instead of individual randomization. Two-week blocks, followed by a washout period of one week will be assigned to either the control or intervention group. Thus, if a delirium episode is detected during a 2-week block allocated to control, this patient and their caregiver will be assigned to the control group and vice versa. Participants will not be informed of the present allocation of the 2-week block of time until after they have consented to the study. Delirium episodes detected during the 1-week wash out period will not be randomized or included in the study.

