For hypothesis H2 on adverse clinical complications following onset of delirium, a combined outcome measure will be used (mention in the hospital chart of sternal wound dehiscence, a fall, respiratory tract infection, or accidental removal of urinary catheter, drain, arterial line or endotracheal tube = yes/no) and groups will be compared using a χ^2^ test.

Student’s T-tests for independent groups will be used for hypothesis involving continuous variables H3 on length of ICU and total hospital stay, H4 on psycho-functional recovery 1 month after the onset of delirium, H5 on caregiver’s anxiety level, and H6 relative to caregiver’s sense of self-efficacy. The planned treatment for missing data for hypotheses H3 to H6 is assigning the value corresponding to the group mean.

Assumptions underlying the planned models will be checked and alternative methods may be used if more appropriate. A significance level of 0.05 will be used for all analyses.

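### Two-week blocks of time are randomised, but the secondary efficacy analyses treat dyads as independent; the recruitment forecast does not reconcile with its own inputs or the washout schedule

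*Protocol article*

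**What the plan says.** **Allocation.** Under Randomization, the protocol article says that to limit contamination "randomization of blocks of time will be used instead of individual randomization". It adds: "Two-week blocks, followed by a washout period of one week will be assigned to either the control or intervention group". Intake stops in the washout: "Delirium episodes detected during the 1-week wash out period will not be randomized or included in the study". The Discussion (Study limits) confirms that one envelope is opened at the start of each block, so there is one assignment per block.

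**Analysis.** Statistical methods names a repeated-measures ANCOVA within a mixed model for H1 and a χ² test for H2. For the rest, "T-tests for independent groups will be used for hypothesis involving continuous variables H3 on length of ICU and total hospital stay", and likewise for H4 to H6. All use a 0.05 level. The only reason given for the mixed model is to keep patients with missing days in the analysis. No analysis mentions the time block.

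**Forecast.** Anticipated recruitment time starts from volume ("On average, 28 patients per week undergo CABG surgery or cardiac valve surgery") and incidence ("A 40% incidence of delirium is estimated, which represents approximately 11 patients weekly"). It takes a past study in the same hospital that "showed a recruitment rate of 30" per cent, and concludes that "one to two dyads weekly is expected and a total of 20 weeks is planned to reach a sample size of 30 dyads".

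**The concern.** Randomising blocks of calendar time makes this a cluster-randomised design with few clusters. Dyads in the same fortnight share staff, ward workload and season, so their outcomes may be correlated. A test that counts 30 independent dyads then takes its precision from the wrong unit, and one unusual fortnight can look like a treatment trend. The pilot is meant to show trends and to build a larger trial. An analysis that leaves out the block also gives no estimate of the between-block variance, which that trial would need if it kept this allocation.

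The forecast is a separate matter. Recruitment time is a feasibility indicator in Table 4, and observed accrual cannot be judged against a planned rate whose basis is unclear.

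**Working it through.** **1. The plan's own figures.** Consent precision: 1.96 × √(0.75 × 0.25 / 30) = 0.155, so ±15.5% reproduces. Recruitment: 20 weeks × 1.5 (midpoint of one to two) = 30, so the target reproduces if the rate applies to all 20 calendar weeks. The ends of the range give 20 and 40.

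**2. Number of blocks.** A cycle of two open weeks and one closed week, starting with a block, has 14 open weeks in 20. That is 7 blocks, which can only split unequally (for example 4:3). Ten blocks take 9 × 3 + 2 = 29 weeks.

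**3. Effect of ignoring the block.** The article gives no ICC, so a range is assumed. Design effect = 1 + (m − 1) × ICC, with m = 30/7 = 4.29 or 30/10 = 3. The true standard error is the dyad-level one multiplied by √(design effect). Type I error is from simulation of the plain t-test with normal outcomes, no true effect, near-equal block sizes and arms split 4:3 or 5:5.

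| ICC (assumed) | 7 blocks: design effect | SE ratio | Type I error | 10 blocks: design effect | SE ratio | Type I error |
|---|---|---|---|---|---|---|
| 0 | 1.00 | 1.00 | 5.0% | 1.00 | 1.00 | 5.0% |
| 0.02 | 1.07 | 1.03 | 5.8% | 1.04 | 1.02 | 5.4% |
| 0.05 | 1.16 | 1.08 | 7.0% | 1.10 | 1.05 | 6.1% |
| 0.10 | 1.33 | 1.15 | about 9% | 1.20 | 1.10 | 7.4% |
| 0.20 | 1.66 | 1.29 | about 13% | 1.40 | 1.18 | 10.2% |

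**4. Degrees of freedom.** A dyad-level t-test has 30 − 2 = 28 df (critical value 2.05). A block-level comparison has 7 − 2 = 5 df (2.57) or 10 − 2 = 8 df.

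**5. Separating clustering from the cost of few blocks.** The dyad-level 95% half-width with 15 per arm is 2.05 × √(1/15 + 1/15) = 0.75 SD. The block-level half-width with 7 blocks at ICC 0 is 2.57 × √[(1/4 + 1/3) / 4.29] = 0.95 SD. The ratio is 0.95 / 0.75 = 1.27. So 27% of widening comes from 5 df and the 4:3 split, before any clustering. The part due to clustering is the SE ratio in the table.

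**6. Forecast against its inputs.** 28 × 0.40 = 11.2 patients with delirium per week; × 0.30 = 3.36 dyads per week. Spread over the two-in-three open fraction this is 3.36 × 2/3 = 2.24 per calendar week. Neither figure is one to two.

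| Reading of the rate | Dyads in 20 weeks | Calendar weeks to 30 dyads |
|---|---|---|
| 1 per open week | 14 | 44 |
| 1.5 per open week | 21 | 29 |
| 2 per open week | 28 | 22 |
| 1.5 per calendar week | 30 | 20 |
| 3.36 per open week (the stated inputs) | 47 | 13 |

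Reaching 30 in 14 open weeks needs 30/14 = 2.14 per open week.

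**The case against.** The article says that the study is not powered for statistical testing, that efficacy results are preliminary, and that other methods may be used once assumptions have been checked. The primary aims are analysed descriptively, and the consent indicator is one pooled proportion, not a comparison of arms. This stands, and it limits how serious the point is. It does not remove it: the article still fixes named tests, a 0.05 level and post-hoc tests that depend on significance, and the general clause on other methods never mentions blocks.

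Three stronger readings are tempting, and the document does not support them.

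- A reader might infer that the planned intervals and p-values are certainly too optimistic. That requires a positive within-block correlation, which the article neither states nor rules out. At a small ICC, with three or four dyads per block, the inflation is modest.
- A reader might take the whole gap between a dyad-level and a block-level interval as the error in the plan. Step 5 shows that much of it is the price of few degrees of freedom.
- A reader might infer that 30 dyads cannot be reached in 20 weeks. That holds only if one to two is a rate per open week. As a calendar-week average the midpoint gives exactly 30, and the stated inputs give about 47 in 14 open weeks. Since the stated rate lies below what the inputs imply, an unstated allowance for closed weeks cannot be excluded.

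**Conclusion.** The mismatch between the randomised unit and the analysed unit is plain in the text and affects all six secondary hypotheses. Its size depends on an ICC that the article does not give. The t-test simulation bears directly on H3 to H6; for H1 and H2 the direction is the same, but the size was not simulated.

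The forecast is unreconciled rather than shown to fall short: the inputs, the stated rate and the washout schedule do not fit together, and the article does not say whether the rate is per open or per calendar week.

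Both matters should be fixed. Neither undermines the pilot's main purpose, because the primary acceptability and feasibility aims do not rest on these tests.

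**What to change.** **Analysis.** State that the two-week block is the randomised unit.

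- For H1 and H3 to H6, add a random block effect with a small-sample degrees-of-freedom correction such as Kenward–Roger, or compare block means with a t-test on (blocks − 2) df. With so few blocks the between-block variance may be estimated as zero, so the block-means comparison is a useful fallback to pre-specify.
- For H2, compare block-level proportions.
- Report the block ICC with its uncertainty, which will be wide, for planning the larger trial.

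**Forecast.** Give the expected rate per open week, explain how it follows from the 3.36 per week that the inputs imply, and restate the recruitment period and number of blocks. An even number is preferable. For example, at 1.5 per open week, 30 dyads need 20 open weeks, or 10 blocks over 29 weeks, which allows a 5:5 split and 8 df instead of 5.

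**Cost.** The analysis change is wording only and needs no new data beyond recording each dyad's block. Intervals become wider, partly because block-level df are few. The recruitment period may lengthen, depending on what the stated rate means.
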